## Abstract

**Background:**

Hormone replacement therapy (HRT) is widely used and has proven benefits for women with menopausal symptoms. An increasing number of women with cancer experience menopausal symptoms but the safety of HRT use in women with cancer is unclear. There are particular concerns that HRT could accelerate cancer progression in women with cancer, and also that HRT could increase the risk of cardiovascular disease in such women. Therefore, our primary aim is to determine whether HRT use alters the risk of cancer-specific mortality in women with a range of common cancers. Our secondary objectives are to investigate whether HRT alters the risk of second cancers, cardiovascular disease, venous thromboembolism and all-cause mortality.

**Methods:**

The study will utilise independent population-based data from Wales using the SAIL databank and Scotland based upon the national Prescribing Information System. The study will include women newly diagnosed with common cancers from 2000 to 2016, identified from cancer registries. Women with breast cancers will be excluded. HRT will be ascertained using electronic prescribing in Wales or dispensing records in Scotland. The primary outcome will be time to cancer-specific mortality from national mortality records. Time-dependent cox regression models will be used to calculate hazard ratios (HR) and 95% confidence intervals (95% CIs) for cancer specific death in HRT users compared with non-users after cancer diagnosis after adjusting for relevant confounders, stratified by cancer site. Analysis will be repeated investigating the impact of HRT use immediately before cancer diagnosis. Secondary analyses will be conducted on the risk of second cancers, cardiovascular disease, venous thromboembolism and all-cause mortality. Analyses will be conducted within each cohort and pooled across cohorts.

**Discussion:**

Our study will provide evidence to inform guidance given to women diagnosed with cancer on the safety of HRT use and/or guide modifications to clinical practice.

## Background

Menopausal hormone replacement therapy (HRT) is widely used globally [1] and has been shown to reduce menopausal related vasomotor symptoms (hot flashes, flushing, and night sweats) and urogenital atrophy [2]. HRT preserves bone mass and is approved by the Food and Drug Administration to prevent postmenopausal osteoporosis [3]. It has also been shown to reduce joint pain, mood swings, sleep disturbances and improve quality of life [2]. Consequently, it has been acknowledged that a reluctance to treat menopausal symptoms can cause unnecessary suffering [4, 5].

### Use of HRT in women with cancer

An increasing number of women with cancer experience menopausal symptoms. HRT is contraindicated in patients with breast cancer and oestrogen-dependent cancers [3, 6, 7] but not in patients with other cancers and authors have argued against the denial of HRT in these patients except when based upon evidence, given the benefits of HRT [8]. Numerous researchers have made recommendations, based upon limited evidence, for and against the use of HRT in patients with cancer depending upon the site of their cancer [8–10].

### HRT and cancer-specific mortality

Various studies have provided evidence suggesting that oestrogen may accelerate the progression of certain cancers. For instance, preclinical studies suggest that oestrogen stimulates growth in bladder [11] and gastric cancer cell lines [12] and lung cancer mouse models [13]. Also, observational studies have shown increases in the risk of glioma and meningioma with use of oestrogen only HRT [14] and the Women’s Health Initiative trial showed a marked increase in death from lung cancer in the oestrogen plus progestin group compared with placebo (HR 1.71, 95%CI 1.16 2.52) [15]. Despite this suggestive evidence, there have not yet been any epidemiological studies of HRT use after bladder, gastric or brain cancer and survival. Although three epidemiological studies have investigated HRT use before lung cancer diagnosis and survival, their results were conflicting [16–18] and none investigated HRT use after diagnosis.

The role of oestrogen in cancer is complex, however, and there is contrasting evidence that oestrogen could delay cancer progression at several cancer sites. For instance, preclinical studies have shown that oestrogen inhibits cell growth and/or induces apoptosis in oesophageal adenocarcinoma [19] and malignant melanoma cell lines [20]. HRT use is associated with a reduced risk of various cancers including liver [21], non-Hodgkin lymphoma [22], and colorectal cancer [23]. A number of studies have investigated hormone replacement therapy after colorectal cancer [24, 25] and melanoma [26, 27] but epidemiological evidence at other cancer sites is sparse. For instance, HRT before diagnosis was associated with reduced mortality in 234 patients with primary liver cancer [21], but HRT after diagnosis was not investigated and in a study of 130 leukaemia patients no excess recurrences were observed in HRT users [28].

### HRT and cardiovascular disease

Studies in the general population have observed that women taking HRT have increased risks of various cardiovascular diseases including coronary heart disease [29], stroke [30] and venous thromboembolism (VTE) [31], particularly in the first years of use [29]. VTE is of particular concern as cancer patients are already at increased risk [32] and it is a common cause of death in cancer patients [33]. Despite this evidence, the risk of cardiovascular disease, and VTE, in cancer patients using HRT has not been investigated previously in large epidemiological cohorts.

### Aims

Our primary aim is to determine the association between HRT use and the risk of cancer-specific mortality in women with a range of common cancers. Our secondary aims are to determine the association between HRT and risk of all-cause mortality, second cancers, cardiovascular disease and VTE in women with cancer.

## Methods/design

### Data sources

The study will utilise the Scottish National Prescribing Information System (Scotland) [34] and the SAIL databank (Wales) [35]. Data sources were selected because they have high quality cancer registry data linked to mortality and prescribing or dispensing data (see Table 1 for details).

**Table 1 Tab1:** Characteristics of included cohorts

Country	Cancer data source	Diagnosis years	Medication data source	Outcome data source	End follow-up	Outcome
Wales (SAIL databank)	Welsh Cancer Intelligence and Surveillance Unit (National Cancer registry for Wales)	2000 to 2016	Primary Care GP dataset (GP prescription records)	Annual District Death Extract	2019	Cancer-specific death
Scotland (eDRIS)	Scottish Cancer Registry	2009 to 2016	Prescribing Information System (dispensed medications)	National Records of Scotland Death Records	2019	Cancer-specific death

### Cohorts

Population-based cohorts of newly diagnosed, from 2000 to 2016, incident female cancer patients aged 40 to 79 will be identified within each data source. The eighteen most common female cancers, excluding breast cancer (as HRT is generally contraindicated in breast cancer patients), will be investigated including: lung, colorectal, cervical, uterine, malignant melanoma, ovarian, non-Hodgkin’s lymphoma, pancreas, kidney, leukaemia, oral, bladder, oesophagus, thyroid, multiple myeloma, brain, gastric and liver. Patients previously diagnosed with other invasive cancer diagnoses (apart from non-melanoma skin cancer) will be excluded.

### Exposure

HRT use will be ascertained from electronic general practitioner (GP) prescribing records (Wales) or dispensing records (Scotland). We will capture both the route of administration (oral, transdermal, vaginal, injection or implant) and type of HRT including oestrogen-only (conjugated equine oestrogen and estradiol) and combined oestrogen with progestogen preparations (oestrogen with medroxyprogesterone acetate, dydrogesterone, norethisterone acetate, norgestrel/levonorgestrel, or drospirenone).

### Outcome

The primary outcome will be cancer-specific mortality (based upon cancer as the underlying cause of death) from national mortality records (see Table 1). Secondary outcomes of all-cause mortality (from mortality records), any second cancer (and by type, from cancer registry records), and cardiovascular disease (from hospital admissions data or mortality records) including separately coronary heart disease, stroke, VTE and any cardiovascular disease (based upon coronary heart disease or stroke), will also be investigated.

### Covariates

The following covariates will be identified: age, year, ethnicity, stage (from cancer registry records), cancer treatment (including radiotherapy, chemotherapy and surgery, from cancer registry records), grade (from cancer registry records), relevant comorbidities (including Charlson comorbidity conditions, from hospital admissions in Scotland and GP records and hospital admissions in Wales), medication use (including aspirin, statins and other medications associated with cancer survival), hysterectomy/oophorectomy (from hospital admissions in Scotland and hospital admissions and GP records in Wales), family history of cancer (from GP records, not available in Scotland), deprivation (based upon the relevant Index of Multiple Deprivation [34, 35]) and smoking and Body Mass Index (BMI from GP records, not available in Scotland).

### Statistical analysis

Two main analyses will be conducted investigating HRT use after diagnosis and immediately before diagnosis.

In the analysis of HRT use after diagnosis, patients will be followed from 6 months after cancer diagnosis to cancer-specific mortality (censored on death from other causes or end of follow-up). Consequently, patients who died from any cause in the first 6 months after cancer diagnosis will be excluded as it seems unlikely that HRT use after diagnosis could impact upon such deaths (in sensitivity analyses this duration will be varied, described later). HRT use will be modelled as a time varying covariate to avoid immortal time bias [36], i.e. patients will be considered non-users and then users after a lag of 6 months after their first HRT prescription. A lag is recommended in studies of medication use and cancer survival [37] as it moves the exposed period forward which is more likely to reflect when the medication will may have an impact. A dose-response analysis will be conducted by duration of use based upon daily defined doses (DDDs) and number of prescriptions. An individual will be considered a non-user prior to 6 months after first HRT use, a user of 0 to 1 year of prescriptions from 6 months after first prescription to 6 months after their 12th prescription (or 365th DDD) and a greater user after this time. Time-dependent cox regression models will be used to calculate hazard ratios (HRs), and 95% confidence intervals (CIs), for HRT use after cancer diagnosis adjusting for age, year, ethnicity, stage, cancer treatment, grade, comorbidities, prior hysterectomy/oophorectomy, medication use (as time-varying covariates) and deprivation. A two-stage analysis procedure using random effects models will be conducted to pool results across cohorts [38]. Separate analyses will be conducted by type and route of administration of HRT.

In the analysis of HRT before diagnosis, cancer patients will be followed from diagnosis to cancer-specific mortality. HRT use will be identified in the 18 months before diagnosis excluding HRT use in the six months immediately before diagnosis, as depending upon the cancer drug use can increase in this period due to cancer symptoms [39]. Cox regression models will be used to calculate HRs and 95% CIs for cancer-specific death in HRT users compared with non-users. Age, year, ethnicity, comorbidities, prior hysterectomy/oophorectomy and medication use before diagnosis will be included in these cox regression models to calculate adjusted HRs and 95%CIs. Stage, grade and cancer treatments will be excluded from the models investigating HRT before diagnosis, as these could lie on the causal pathway. As before two-stage methods will pool results across cohorts.

A number of additional analyses will be conducted. First, the main analysis will be repeated additionally adjusting for characteristics not available in both cohorts e.g. family history, smoking and BMI (only available in Welsh data). An analysis will be conducted restricted to women over age 55 (i.e. post-menopausal women) and an analysis will be conducted widening the age groups to include younger women aged 18 to 40 (Scottish data). An analysis of HRT after diagnosis will be conducted using a new-user design i.e. restricting analyses to cancer patients who did not use HRT before diagnosis [40], and after adjustment for HRT before diagnosis. A separate analysis will be conducted investigating the timing of HRT initiation after cancer diagnosis. Analyses of HRT after diagnosis will be conducted varying the lag from 6 months to 1 and 2 years.

The primary analysis strategy will be repeated for the secondary outcome of all-cause mortality and second cancers. A different analysis strategy will be used to investigate the secondary outcome of cardiovascular disease and VTE. In these analyses current use of hormone replacement therapy after cancer diagnosis will be modelled as a time-varying covariate. Patients will become a current user upon the date of each hormone replacement therapy prescription, and remain a user for the duration of the prescription, based upon the daily defined dose, plus 30 days to account for any residual effect. The exposure period from the end of one prescription plus 30 days to the start of the next will be allocated to past use. Cox regression models will then be used to calculate HRs and 95% CI for cardiovascular disease overall and by type comparing hormone replacement therapy current use and past use to non-users, adjusting for the confounders mentioned previously.

In general, multiple imputation will be used to impute missing values particularly for stage, smoking and BMI. As recommended cancer-specific death status and cumulative hazard will be included in imputation models [41], along with exposure and confounder variables and results will be combined using Rubin’s rules. STATA 16 will be used for all analyses.

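### The HRT-after-diagnosis models do not use histological type, so sites that mix subtypes of very different prognosis may keep residual confounding

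*Protocol article*

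**What the plan says.** The Covariates section begins "The following covariates will be identified: age, year, ethnicity, stage (from cancer registry records), cancer treatment (including radiotherapy, chemotherapy and surgery, from cancer registry records" and later adds "grade (from cancer registry records", again from the registry. These are the items on the list that describe the index tumour or its treatment. Under Statistical analysis, the after-diagnosis model is fitted "adjusting for age, year, ethnicity, stage, cancer treatment, grade, comorbidities, prior hysterectomy/oophorectomy, medication use (as time-varying covariates) and deprivation".

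The Abstract says that hazard ratios are estimated "after adjusting for relevant confounders, stratified by cancer site", and the Cohorts section lists eighteen sites, ending with "leukaemia, oral, bladder, oesophagus, thyroid, multiple myeloma, brain, gastric and liver". No site has its own covariate set. The additional analyses vary age range, lag, prior HRT use, timing of initiation and extra Welsh covariates; none is by tumour type.

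On missing data: "In general, multiple imputation will be used to impute missing values particularly for stage, smoking and BMI". No exception is made by site.

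The Background argues partly by subtype. It cites preclinical evidence that "oestrogen inhibits cell growth and/or induces apoptosis in oesophageal adenocarcinoma", and for brain it names glioma and meningioma separately.

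**The concern.** Several of the eighteen sites are not one disease. Acute and chronic leukaemia, small-cell and other lung cancer, squamous cancer and adenocarcinoma of the oesophagus, and the various brain tumour types differ greatly in prognosis. A model that pools them adjusts for that difference only as far as stage, grade and treatment stand in for it. If HRT users have a different subtype mix from non-users, the site-specific HR carries part of the subtype effect, in a direction that cannot be known beforehand.

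A second issue is stage at sites where the conventional solid-tumour scheme does not apply, leukaemia being the clearest. Imputing a value that is unrecorded because it is undefined adds no information on severity, yet the output would look stage-adjusted.

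At stake is the interpretation of the primary HR at the mixed sites. For the oesophagus, there is also the question of whether the analysis can address the tumour type for which the Background cites evidence.

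**Working it through.** **1. What is in the model.** Setting the Covariates list beside the after-diagnosis model gives the same three tumour-related items: stage, grade and treatment (surgery, radiotherapy, chemotherapy). Histology, morphology and subtype appear in neither place, nor among the additional analyses. The list is open-ended for comorbidities and medicines but not for tumour characteristics, so this is a stated choice.

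**2. The plan's own effect sizes, as a yardstick.** Inputs from the Sample size calculation section: 7% exposed, 5% level (taken as two-sided), Schoenfeld's method. Power = Φ(|ln HR| × √(d × 0.07 × 0.93) − 1.96), where d is the number of cancer deaths.

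- Colorectal, d = 6820: √(6820 × 0.0651) = 21.07. HR 1.15 gives Φ(0.1398 × 21.07 − 1.96) = 83.8%; HR 0.85 gives 92.9%.
- Gastric, d = 1181: √(1181 × 0.0651) = 8.77. HR 1.45 gives Φ(0.3716 × 8.77 − 1.96) = 90.3%.

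All agree with the stated power of over 80%. The article gives no detectable effect for leukaemia, myeloma, brain, lung or oesophagus.

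**3. Size of a possible bias.** For a binary aggressive subtype left out of the model, with a true HRT effect of 1.00:

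apparent HR = (1 + pu(R − 1)) / (1 + pn(R − 1))

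Here pu and pn are the subtype's shares in users and non-users, and R is its hazard ratio for cancer death. None of the three is in the documents; all values below are assumptions. With pn = 0.35:

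| pu | R = 3 | R = 5 |
|---|---|---|
| 0.35 | 1.70/1.70 = 1.00 | 2.40/2.40 = 1.00 |
| 0.50 | 2.00/1.70 = 1.18 | 3.00/2.40 = 1.25 |
| 0.25 | 1.50/1.70 = 0.88 | 2.00/2.40 = 0.83 |

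Other assumed shares, with R from 2 to 5:

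- 45% of users against 55% of non-users: 0.94 to 0.88.
- 40% against 60%: 0.88 to 0.77.
- 50% against 50%: 1.00 throughout.

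These are crude factors. They allow nothing for the adjustment for grade, treatment and age, nor for the exclusion of deaths in the first 6 months, all of which could shrink them.

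**4. Stage and imputation.** The missing-data paragraph singles out stage for imputation and exempts no site. The article does not say how either registry codes stage for leukaemia or myeloma. That it is undefined for leukaemia is general clinical knowledge; for myeloma it depends on what the registry records.

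**The case against.** A reader might go further and infer that the HRs for leukaemia, myeloma and brain are in effect unadjusted for severity. The documents do not support that, for three reasons. Grade is in the model and brain tumours are graded, so what is missing for brain is tumour type. Treatment is in the model at every site and partly reflects both severity and subtype. And nothing in the article shows that stage will be empty at these sites. For myeloma, moreover, a histology variable would bring no evident gain.

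The mechanism that comes first to mind, intensive leukaemia treatment causing ovarian failure and so leading to HRT, runs largely through treatment, which is adjusted for. It also needs premenopausal women, whereas the cohort is aged 40 to 79 and one additional analysis is restricted to women over 55. This weakens the example but does not settle the matter: the three broad treatment types listed are an incomplete proxy for subtype.

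The exclusion of deaths in the first 6 months and the lags of 6 months, 1 year and 2 years reduce the weight of the most rapidly fatal disease. They do not equalise subtype among the survivors.

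The yardstick of 1.15 or 0.85 belongs to colorectal cancer. At gastric cancer the stated detectable HR is 1.45, and an illustrative bias of 1.25 falls well short of it. So the illustration does not show that bias would reach the detectable effect at the mixed sites.

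Finally, a condensed article may leave site-specific detail to a fuller plan, the imputation sentence is qualified as general, and the adenocarcinoma evidence is background, not a stated hypothesis. That is fair, and it makes separate reporting of that type a recommendation and not the repair of a contradiction. It does not remove the main point, because the tumour covariates are listed explicitly.

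**Conclusion.** The point holds for the HRT-after-diagnosis models and should be addressed, though it is not a fatal flaw. Tumour-related adjustment is limited to stage, grade and treatment at all eighteen sites, and histological type is not used. At sites with distinct subtypes this leaves residual confounding if, and only if, subtype is related to HRT use given the covariates already in the model.

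The documents do not quantify that relation. With the aggressive subtype at 35% of non-users and 25% to 50% of users, and with 3 to 5 times the hazard, the apparent HR runs from 1.00 with equal shares to about 0.83 in one direction and 1.25 in the other, before any offset from grade and treatment. A wider assumed gap would go beyond this range. These figures show what is possible; they do not estimate the bias in this study.

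How stage will be handled where it is undefined is a smaller, separate matter that needs a sentence in the plan. The before-diagnosis model lies outside the point: it leaves out stage, grade and treatment on purpose, as possible mediators.

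**What to change.** 1. In the after-diagnosis models, add a site-specific histology group built from cancer registry morphology codes, as strata or covariates, at sites with distinct subtypes: for example acute versus chronic leukaemia, small-cell versus other lung cancer, squamous cancer versus adenocarcinoma of the oesophagus, and brain tumour type.
2. Report oesophageal adenocarcinoma as a subgroup, since the Background cites evidence for that type.
3. Where conventional stage is not defined for a site (leukaemia, and myeloma if the registry records none), leave it out of both the adjustment and the imputation model for that site. State as a limitation any site left without a severity measure.
4. Leave the before-diagnosis model unchanged on this point.

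The cost is a short addition to the text, a grouping of codes fixed before analysis, and a few extra parameters, which will be felt mainly at small sites; sparse groups there may have to be merged. It assumes that morphology codes come with the registry extracts that supply stage and grade. The article does not say so, and it should be confirmed for both Wales and Scotland.

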### Sample size calculation

Sample size calculations were conducted based upon the number of cancer cases in published studies from Scotland [42, 43], and in Wales based upon published counts of cases from the Welsh Cancer Intelligence and Surveillance Unit assuming 90% have GP linked data (provided by SAIL databank). The number of deaths was estimated based upon survival at 6 months and 5 years from English published female survival curves [44]. In sample size calculations we estimated that 7% of female cancer patients would use HRT after diagnosis similar to published reports (e.g. 5% of a Swedish colorectal cancer cohort used HRT after diagnosis [25], and 9% of a Danish melanoma cohort used HRT after diagnosis [26]).

For instance, we estimate there will be 22,000 colorectal cancer cases diagnosed in Scotland (diagnosed 2009 to 2016) and Wales (diagnosed 2000 to 2016), of whom, approximately 20% (4400) will die within 6 months (and be removed from analysis of HRT after diagnosis) and a further 31% (6820) will die within 5 years. Therefore, based on a cohort of 17,600 colorectal cancer patients and 6820 cancer-specific deaths, we would have over 80% power to detect, as significant at the 5% level, a HR for cancer-specific mortality of 1.15 (or 0.85) for HRT users after diagnosis (i.e. we could detect an increased risk of cancer-specific mortality in HRT users of 15%) using Schoenfeld’s method [45]. Similarly, in gastric cancer patients, we anticipate 3300 patients and 1181 cancer-specific deaths in the analysis of HRT after diagnosis and therefore we would have over 80% power to detect, as significant at the 5% level, a HR for cancer-specific mortality of 1.45 for HRT users after diagnosis. A similar analysis is being conducted in England using QResearch and we anticipate pooling results across the three cohorts which will further increase power.

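### The stated colorectal power at HR 1.15 is that of a common-effect analysis, not of the planned two-cohort random-effects pooling, which gives about 72–74% under common estimators

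*Protocol article*

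**What the plan says.** In the protocol article, the Statistical analysis section fixes how the national results are combined after the analysis of HRT use after diagnosis: "A two-stage analysis procedure using random effects models will be conducted to pool results across cohorts [38". It carries this over to HRT use before diagnosis: "As before two-stage methods will pool results across cohorts". Table 1 lists two cohorts, Wales and Scotland. The article names neither the between-cohort variance estimator nor the reference distribution for the pooled test.

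The Sample size calculation section treats the two countries as one source. It starts from "22,000 colorectal cancer cases diagnosed in Scotland (diagnosed 2009 to 2016) and Wales (diagnosed 2000 to 2016", removes early deaths, and then works "based on a cohort of 17,600 colorectal cancer patients and 6820 cancer-specific deaths". From this it concludes that "we would have over 80% power to detect, as significant at the 5% level, a HR for cancer-specific mortality of 1.15 (or 0.85"), obtained "using Schoenfeld’s method [45"]. The exposure assumption is that "we estimated that 7% of female cancer patients would use HRT after diagnosis". A second example gives 1181 gastric cancer deaths and over 80% power at HR 1.45. The section also expects to pool later with an English cohort, whose deaths are not in these counts.

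**The concern.** Schoenfeld's formula on the summed deaths gives the power of one analysis of one cohort. It also holds for an inverse-variance average of two cohort estimates that share one true HR. A random-effects pool of two estimates behaves differently. It must estimate a between-cohort variance from a single difference. By chance that estimate is above zero in about a third of datasets even when the true variance is zero, and each time it widens the interval.

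The article therefore states both an analysis and a power figure, and the figure belongs to another analysis. This matters most at HR 1.15, because the section spells that effect out as the increase in risk it can detect, and harm is the study's safety question. A reader of a null pooled result would credit the study with more sensitivity to a 15% increase than the planned method may have.

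**Working it through.** **Inputs from the Sample size calculation section.** Deaths D = 6820 (colorectal) and 1181 (gastric), taken as given; exposed share p = 0.07; 5% level, taken as two-sided because sidedness is not stated; HR 1.15, 0.85 and 1.45.

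**Assumptions not in the article.** The split of deaths between countries (50:50 to 70:30), the between-cohort SD of the log HR (0, 0.05, 0.10), the variance estimator and the reference distribution.

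**Step 1: reproduce the stated figure.** The information is D·p·(1−p) = 6820 × 0.07 × 0.93 = 443.98, so the common-effect standard error is 1/√443.98 = 0.0475. At HR 1.15, ln(1.15) = 0.1398 and the standardised effect is 0.1398 × √443.98 = 2.945. Power = Φ(2.945 − 1.960) = 83.8%. The same formula gives 92.8% at HR 0.85 and 90.3% for gastric cancer at HR 1.45. The stated figure of over 80% reproduces in each case.

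**Step 2: the planned pooling, equal split, no true heterogeneity.** With two cohorts of equal variance, Cochran's Q has 1 df and is independent of the pooled mean. The DerSimonian-Laird standard error is then the common-effect one times √max(1, Q), so

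power = E[Φ(2.945 − 1.960·√max(1, Q))], Q ~ χ²(1).

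- Q ≤ 1 (probability 0.683): the variance estimate is zero and power is 83.8%.
- Q > 1 (probability 0.317): the interval widens and average power is 51.1%.
- Total: 0.683 × 0.838 + 0.317 × 0.511 = 0.734.

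**Step 3: other splits and heterogeneity.** Pairs of log HRs were simulated with variances 1/(deaths × 0.07 × 0.93) plus SD², pooled by DerSimonian-Laird and tested against the normal distribution (500,000 pairs per setting).

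| Setting | 50:50 | 60:40 | 70:30 |
|---|---|---|---|
| Colorectal, HR 1.15, SD 0 | 73% | 73% | 72% |
| Colorectal, HR 1.15, SD 0.05 | 64% | 63% | 62% |
| Colorectal, HR 1.15, SD 0.10 | 49% | 49% | 49% |
| Colorectal, HR 0.85, SD 0 | 84.1% | 83.7% | 82.5% |
| Colorectal, HR 0.85, SD 0.05 | 74% | 73% | 72% |
| Gastric, HR 1.45, SD 0 | 81% | 80% | 79% |

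With SD 0 the type I error is about 3.8%, so the test is conservative. The HR with 80% power moves to about 1.165 (50:50) or 1.17 (70:30).

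**Step 4: dependence on the estimator (HR 1.15, SD 0).** REML gives 73.8% (50:50) and 72.6% (65:35). Maximum likelihood gives about 81% at both splits. Hartung-Knapp with t on 1 df gives about 18%.

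**The case against.** Several points on the other side are sound.

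- **The shortfall is not general.** A reader might infer that the study lacks its stated power throughout. The article's own figures do not support that. At HR 0.85, which it also names, power with no heterogeneity stays above 80% at these splits, and the gastric claim roughly holds.
- **The 73% is conditional.** The article says only random effects. A condensed article may leave the estimator to a fuller document, and maximum likelihood would keep the stated figure. This limits the claim. It also shows that the power sentence cannot be checked until the estimator is fixed.
- **The practical shift is modest.** With no heterogeneity the detectable HR moves from 1.15 to about 1.17. Intervals are 17–20% wider on average, but in about 68% of datasets they do not change at all. The cohort size is set by the registries, so recruitment does not depend on this figure.
- **A third cohort is expected.** If England added 3,410 to 20,000 colorectal deaths (an assumption), DerSimonian-Laird power at HR 1.15 would be 89–97% with SD 0 and 78–88% with SD 0.05. The stated figure, however, rests on the two-country deaths alone.
- **Random effects is a defensible choice.** A reader might infer that it is an error with two cohorts and that fixed effects must replace it. The cohorts differ by design: prescriptions against dispensed drugs, different diagnosis years, different comorbidity sources. Random-effects intervals do under-cover the overall mean HR when heterogeneity is real (92% at SD 0.05, 84% at SD 0.10, 50:50 split), but the fixed-effects interval covers it worse (88% and about 73%).

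**Conclusion.** The point holds in limited form: the over-80% figure at HR 1.15 makes no allowance for the pooling method the article names. Under DerSimonian-Laird or REML with a normal test, two cohorts and no true heterogeneity, it overstates power by about 10 to 12 percentage points (83.8% against about 72–74%). Real heterogeneity widens the gap. The size rests on the assumed event split, to which it is not sensitive between 50:50 and 70:30, and on the estimator, to which it is very sensitive. The finding concerns a stated power figure. It does not show that the pooling model is wrong, or that the claims at HR 0.85 or for gastric cancer fail materially when the cohorts agree.

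**What to change.** Name the between-cohort variance estimator and the reference distribution in the Statistical analysis section, and restate the two-cohort power for that analysis. For DerSimonian-Laird or REML with a normal test and no heterogeneity, the colorectal sentence would give about 73% power at HR 1.15, or 80% power at an HR of about 1.17. State the assumed event split and add one figure for a plausible SD, such as about 62–64% at SD 0.05. If Hartung-Knapp is intended, say so, because two-cohort power is then about 18%.

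Alternatively, if the sponsor wants the average effect in these two populations, state that estimand and use the inverse-variance fixed-effects average as primary. The over-80% figure then stands. Show both national HRs beside it and keep random effects as a sensitivity analysis. The price is that the result no longer speaks to an overall mean beyond the pooled cohorts.

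Either route costs one or two sentences and no new data.
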